**Review of identifiable medical records: [Note: A waiver of HIPAA Authorization must be requested (2.14.2)]**

The research involves no more than minimal risk to the subjects; [45 CFR 46.116 (d)(1)]

The waiver or alteration will not adversely affect the rights and welfare of the subjects; [45 CFR 46.116 (d)(2)]

The research could not practicably be carried out without the waiver or alteration;[45 CFR 46.116 (d)(3)]

Whenever appropriate, the subjects will be provided with additional pertinent information after participation.[45 CFR 46.116 (d)(4)]

#### **Parental Permission and/or Child Assent**

The research involves no more than minimal risk to the subjects;[45 CFR 46.116 (d)(1)]

The waiver or alteration will not adversely affect the rights and welfare of the subjects;[45 CFR 46.116 (d)(2)]

The research could not practicably be carried out without the waiver or alteration;[45 CFR 46.116 (d)(3)]

Whenever appropriate, the subjects will be provided with additional pertinent information after participation.[45 CFR 46.116 (d)(4)]

#### **Alteration of informed consent process**

The research involves no more than minimal risk to the subjects;[45 CFR 46.116 (d)(1)]

The waiver or alteration will not adversely affect the rights and welfare of the subjects;[45 CFR 46.116 (d)(2)]

The research could not practicably be carried out without the waiver or alteration;[45 CFR 46.116 (d)(3)]

**4.8 Are you requesting an exception to the requirement to obtain informed consent for research involving the evaluation of an “emergency” procedure? Note: This exception allows research on life-threatening conditions for which available treatments are unproven or unsatisfactory and where it is not possible to obtain informed consent.**

No

#### **4.9 Upload all written informed consent documents.**

Draft Consent Forms for editing (attached in IRB form):

Name

Consent Form - Depressed

Consent Form - Non-depressed

Approved Consent Form(s):

Name

Consent Form - Depressed

Consent Form - Non-depressed

**4.10 Will all potential adult subjects be capable of providing direct consent for study participation?**

Yes.

**4.11 At what point will you obtain the informed consent of potential research subjects or their authorized representative?**

After performing certain of the screening procedures, but prior to performing any of the research interventions/interactions.

**4.11.1 Address why you feel that it is acceptable to defer obtaining written informed consent until after the screening procedures have been performed.**

As seen in our previous R34 cohort study where we screened 857 hospitalized HF patients, only 401 (47%) met primary eligibility criteria of NYHA class and PHQ-2 positive. Therefore, it would be an unnecessary burden for the rather sick patients to undergo the entire consent process while the majority will not be protocol eligible. We therefore request to only spend 10-15 minutes with the patient for the screening, and then spend the additional 30-45 minutes required to administer the MoCA, explain the study in detail, and obtain the written consent only with those patients who are eligible. This would also streamline our study's recruitment process, and help us meet our recruitment milestones.

**4.11.2 Taking into account the nature of the study and subject population, indicate how the research team will ensure that subjects have sufficient time to decide whether to participate in this study. In addition, describe the steps that will be taken to minimize the possibility of coercion or undue influence.**

If the patient meets our eligibility criteria, then our study nurse will give the patient the consent document, and offer to return after the patient had time to read the document. Afterwards, the patient will have time to ask the study nurse any questions that may occur when he/she returns to the patient's room. Patients may still request additional time to discuss their participation with family members or friends, and if so the study nurse will come back on a later day to review the consent document. We will train all study nurses in the explanation of the study, and in obtaining consent in a non-coercive manner. Furthermore, we will conduct spot-checks to ensure that no undue influence is exercised on potential study patients.

**4.12 Describe the process that you will employ to ensure the subjects are fully informed about this research study. This description must include the following elements:**

- **who from the research team will be involved in the consent process (both the discussion and documentation);**
- **person who will provide consent or permission;**
- **information communicated; and**
- **any waiting period between informing the prospective participant about the study and obtaining consent**

Each UPMC hospital has an inpatient HF Management Program that HF patients are referred to automatically upon hospital admission through an automated review of their admitting diagnoses, or following admission should the HF diagnosis be uncovered during the hospitalization. Our study cardiologist, [name], will encourage HF Management Program staff and cardiology consult teams to obtain patients' whose ejection fraction is  $\leq 40\%$  to provide verbal HIPAA agreement permitting our nurse-recruiters to confirm their ejection fraction meets study criteria, and if so to approach and explain our study and obtain their patients' consent to undergo our screening procedures. Our study nurses will then screen the patients for eligibility as described in 4.2. If the patient meets eligibility criteria for our study, and remains interested, the study nurse will then explain the study in detail as outlined in the

consent document, answer any questions the patient may have, and give the patient time to consider participation or discuss it with his/her family. If the patient agrees to participate, then they will be asked to sign the informed consent, and the study nurse will document the process. At 2-weeks after hospital discharge a research assessor will call the patient, and establish if the patient is still eligible. At this point the patient can also decide to continue to participate in our study. Only if the patient is still eligible and confirms his continued interest, will he/she be randomized to our study.

**4.13 Are you requesting an exception to either IRB policy related to the informed consent process? For studies involving a drug, device or surgical procedures, a listed physician investigator is required to obtain the written informed consent unless an exception to this policy has been approved by the IRB For all other studies, a listed investigator is required to obtain consent (Note: In order to request an exception to this policy, the study must be minimal risk).**

Yes

**If Yes, provide a justification and describe the qualifications of the individual who will obtain consent:**

We request an exemption to IRB Policy 4.13 because the study involves minimal risk and the study doctors will never prescribe any drugs, devices, or surgical procedures. Requiring a study physician to obtain consent would also make the trial logistically impractical to conduct as we plan to hire study nurses who will enroll study patients from 4-6 UPMC-affiliated hospitals daily during routine weekday business hours.

**4.14 Will you inform research subjects about the outcome of this research study following its completion?**

Yes.

**If Yes, describe the process to inform subjects of the results:**

We will telephone the patient to confirm vital status and mailing address after our trial's 'main outcomes' paper is published, and if the patient is alive mail them a copy of our paper.

## **5.0 – Potential Risks and Benefits of Study Participation**

**5.1 Describe potential risks (physical, psychological, social, legal, economic or other) associated with screening procedures, research interventions/interactions, and follow-up/monitoring procedures performed specifically for this study:**

|                    |                                                                                                                                                                                                                       |
|--------------------|-----------------------------------------------------------------------------------------------------------------------------------------------------------------------------------------------------------------------|
| Research Activity: | Intervention                                                                                                                                                                                                          |
| Common Risks:      | Patients may experience discomfort discussing disturbing symptoms and/or psychosocial concerns.                                                                                                                       |
| Infrequent Risks:  | Breaches in confidentiality involving medical information could impact future insurability, employability, or reproduction plans, or have a negative impact on family relationships, and/or result in stigmatization. |
| Other Risks:       | Disclosure of suicidal behavior and medical problems                                                                                                                                                                  |

|                    |                                                                                                                                                                                                                       |
|--------------------|-----------------------------------------------------------------------------------------------------------------------------------------------------------------------------------------------------------------------|
| Research Activity: | Screening and assessment                                                                                                                                                                                              |
| Common Risks:      | The discussion of personal problems during screening could be stressful, uncomfortable, or embarrassing to some people. They may be falsely labeled as having a mood disorder.                                        |
| Infrequent Risks:  | Breaches in confidentiality involving medical information could impact future insurability, employability, or reproduction plans, or have a negative impact on family relationships, and/or result in stigmatization. |
| Other Risks:       | No Value Entered                                                                                                                                                                                                      |

### 5.1.1 Describe the steps that will be taken to prevent or to minimize the severity of the potential risks:

The risks to study patients are that they may experience discomfort discussing disturbing symptoms and/or psychosocial concerns, and that they may be falsely labeled as having a mood disorder and offered treatment for it. Furthermore, stigmatization surrounding mental illness can make exploration of emotional issues uncomfortable, particularly if the patient has not established a secure relationship with his/her cardiologist and PCP. Still, given the 85% specificity of the PHQ-2/PHQ-9 screening procedure for major depression among patients with CVD, we believe the great majority of our findings will be correct on those patients so identified. The few subjects who are inappropriately diagnosed as having depression may, in fact, have a partly remitted episode or a subsyndromal disorder.

Since these conditions are associated with significant impairment in quality of life, patients so “overdiagnosed” may still benefit from any increased attention provided to them by their PCP or from our interventions. With regard to experiencing discomfort when discussing disturbing psychosocial concerns, our assessor and care manager will advise subjects who are unduly distressed to contact their PCP, or Drs. [name], [name], or [name] to discuss these concerns. Patients may voice medical problems (e.g., chest pain) or suicidal ideation during their telephone encounters with study staff. In case of physical problems, our staff will advise the patient to call their physician right away to first clarify the severity of their medical problems. If a patient voices suicidal ideation, our electronic suicide risk management protocol ([name] et al. 2011) that we have used in our previous studies will be automatically triggered, and the staff will follow its guidelines. Furthermore, we will again establish an on-call system of study psychiatrists who will be available 24/5 for the staff for triage.

All research staff and study investigators will complete the University of Pittsburgh’s on-line training for the ethical conduct of clinical research (<http://www.health.pitt.edu/rpf/>), and we will obtain approval from our University IRB which covers all UPMC clinical facilities prior to the commencement of study recruitment. Detailed descriptions of patient recruitment and informed consent are provided in C3-C4. No patient or physician will be identified in any description or publication of this research.

Confidentiality will be maintained by assigning each study patient a computer-generated identifying number for use in our data files. All data obtained will be kept in locked file cabinets and on password-protected computers with access provided only to designated study personnel to ensure strict confidentiality. Select members of our research team will have electronic access to specific folders that contain de-identified patient data (e.g., database manager and statistician). Identified data will be stored in a separate table with only the database manager, assessor, and care manager having access in accordance with their roles on the project (e.g., to send-out participant payments). No personal information concerning study subjects will be released without their written consent, with the exception should one of our study staff detect active suicidality and/or acute clinical decompensation which will be released only to the

subject’s personal physician(s). We will store paper consent forms, discharge summaries, and other primary data sources in locked files at the Center for Research on Health Care where the investigators’ offices and our Data Center are located with access provided only to designated research personnel. Each study member who is provided with access to our paperless data management system (C16) will be issued a unique, permanent, user identifier (ID), and private password. Both will be needed to confirm one’s identity whenever retrieving or entering data. We will set-up different user profiles that will allow access to relevant sections of the database by job description. Sharing of passwords is strictly forbidden and leaving unattended “open” records strongly discouraged by the use of reminder messages displayed at the time of logging-in to the system and timed automatic log-outs from the system. User accounts for study staff who leave the employment of our research team will be terminated following their last day of work. Routine patient monitoring and quality control reports will only identify patients by study number and the patient’s first name as we did on the weekly monitoring reports generated for all intervention patients enrolled into our CABG study.

To further promote the security and integrity of our data, our paperless data management system will operate on a dedicated computer server in our Data Center behind the UPMC network “firewall” to protect against viruses, eavesdropping, tampering, and unauthorized usage of the system. Our Data Center has expertise in developing HIPAA-compliant software applications and we will work with them to ensure our system is in compliance with all regulations.

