Over a 12-month time period following randomization, the nurse-care manager will call all patients randomized to an intervention arm (“blended” or eUC) on a regular basis, every other week during the acute phase of their intervention (approximately 2-3 months), and then monthly during the “continuation phase” until the end of intervention enrollment, and we expect a median of 14 calls as in our other trials. Should a patient’s symptoms (either depression or HF) worsen during the continuation phase, then the care manager will resume to more frequent calls. If a patient is not interested in the study after the first call, the patient will remain eligible for the blinded assessment calls, but he or she will not receive any more intervention calls by the nurse-care manager. We anticipate most telephone contacts between the nurse-care manager and the patient will be brief (15-20 minutes), unless special circumstances intervene (e.g., the patient expresses suicidal ideations, has questions or side effects regarding pharmacotherapy). For all intervention patients the nurse-care manager will : (1) educate the patient regarding HF and treatment goals (e.g., 20-40 min aerobics 3-5x/week); (2) encourage heart healthy lifestyle (tobacco cessation, sleep, etc.); (3) promote adherence/adjustment of HF pharmacotherapy as prescribed by the patient’s PCP/cardiologist; (4) promote outpatient self-monitoring of weight, BP, diet, and doctor visits; (5) monitor for treatment response and relapse ; and (6) suggest/facilitate PCP/cardiologist/ER referrals when appropriate. The care manager will record above data into our electronic data base and will present these at our weekly case reviews. At these meetings, Drs. [name] (internist), and [name] (study coordinator) will make recommendations regarding their pharmacotherapy for HF, promotion of healthy lifestyles (e.g., exercise, sleep, weight control, and/or referrals to PCP/Cardiologist ER) which the care manager in turn will communicate to the patient.

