As per our University’s IRB guidelines, if any adverse events are identified we will report this information to our IRB, the funding Institute, and forward a report to our DSMB. In this report we will include a summary of adverse event and how we handled each situation. Our paperless data management system will also allow us to track and process each key events (or serious adverse event) through the process of collection, physician adjudication, and presentation to our DSMB faster than if these processes were “carved-out” to an outside organization. In the course of conducting routine telephone assessments or care contacts our blinded assessors and care managers may also encounter HF patients in the process of clinical decompensation (e.g., patient self-report of severe shortness of breath, chest pressure, etc.).

As with our CABG and HF studies, in these events our study staff will advise these patients to telephone their PCP and/or cardiologists ASAP for further advice, present to an emergency room, or call “911” for immediate medical attention given the seriousness and instability of patients with HF. As referral to the local ER may bias our findings towards an increase in the rate or number of hospitalizations in intervention patients, we will record these events to adjust for a confounding of our findings later.

**5.14 What precautions will be used to ensure subject privacy is respected? (e.g. the research intervention will be conducted in a private room; the collection of sensitive information about subjects is limited to the amount necessary to achieve the aims of the research, so that no unneeded sensitive information is being collected, drapes or other barriers will be used for subjects who are required to disrobe).**

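### For chest pain reported on a study call, section 5.1.1 gives physician-first advice and names no emergency option, while 5.13 offers the ER or 911 for an overlapping symptom

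*Protocol*

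**What the plan says.** Section 5.1.1 of the protocol describes how risks to participants are minimised. It foresees that "Patients may voice medical problems (e.g., chest pain) or suicidal ideation during their telephone encounters with study staff". For the physical kind it gives one rule: "In case of physical problems, our staff will advise the patient to call their physician right away to first clarify the severity". For suicidal ideation the same paragraph provides an electronic protocol that starts automatically, and adds that "we will again establish an on-call system of study psychiatrists who will be available 24/5 for the staff for triage". A later paragraph of 5.1.1 mentions acute clinical decompensation, but only as an exception to confidentiality that allows disclosure to the patient's own physicians.

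Section 5.13, the data and safety monitoring plan, says that assessors and care managers may encounter "HF patients in the process of clinical decompensation (e.g., patient self-report of severe shortness of breath, chest pressure, etc". For these patients, "our study staff will advise these patients to telephone their PCP and/or cardiologists ASAP for further advice, present to an emergency room, or call" the emergency number, 911. The purpose and the reason are stated as well: "for immediate medical attention given the seriousness and instability of patients with HF". It then notes: "As referral to the local ER may bias our findings towards an increase in the rate or number of hospitalizations in intervention patients". Such events are to be recorded so that the findings can be adjusted for them.

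Section 2.6 touches the subject twice. One care-manager task in the two intervention arms is to "suggest/facilitate PCP/cardiologist/ER referrals when appropriate". For usual-care patients, the study will tell the doctor if the patient's condition has clearly worsened at an assessment call; chest pain is one of the two examples given.

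**The concern.** Everyone enrolled has an ejection fraction of 40% or less and NYHA class II to IV symptoms (section 3.13). In such patients, chest pain reported by telephone may be an emergency. Section 5.1.1 names that symptom and then has staff send the patient to a physician to find out how serious it is. Followed to the letter, this puts a physician call ahead of emergency action and could delay it. The sponsor's own reason for listing the ER and 911 in 5.13, the instability of these patients, applies equally to chest pain under 5.1.1.

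**Working it through.** No figure in the protocol bears on this, so the check is a comparison of texts.

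| | Section 5.1.1 | Section 5.13 |
|---|---|---|
| Who acts | Study staff | Blinded assessors and care managers |
| Setting | Telephone encounters | Telephone assessments or care contacts |
| Trigger | Physical problems; chest pain is the example | Decompensation; severe shortness of breath and chest pressure are the examples |
| Severity framing | None; the physician is to clarify it | The patient is described as decompensating |
| Action | Call the physician right away | Call the PCP or cardiologist, go to an ER, or call 911 |
| Reference to the other section | None | None |

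1. **Do the two rules reach the same calls?** Yes. Staff and setting coincide, and chest pain and chest pressure overlap as complaints.

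2. **Does the text separate them by severity?** In part. Section 5.13 is framed around decompensation, and 5.1.1 covers physical problems generally. But 5.1.1 attaches no severity to chest pain and passes the judgement of severity to the physician. Staff following 5.1.1 alone therefore reach no step that leads them to 5.13.

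3. **Does the protocol treat chest pain as a lesser complaint?** No. Section 2.6 pairs it with suicidality as an example of marked worsening.

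4. **Do other provisions supply the emergency option within 5.1.1?** They do not:
   - The ER-referral task in section 2.6 belongs to care managers in the two intervention arms.
   - The notice to a usual-care patient's doctor is a real safeguard, but it goes to the physician and is not emergency advice to the patient.
   - The on-call triage in 5.1.1 is psychiatric.
   - Sections 2.5.2 and 5.2 deal with suicidal ideation and delirium.

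5. **Does 5.13 supply it?** Yes. Its wording is not limited by arm, so it covers all four groups. What remains is that 5.1.1 states a narrower rule for an overlapping symptom and does not send the reader to 5.13.

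**The case against.** The strongest reply is that the protocol already has the emergency route. Section 5.13 addresses the same staff, the same calls and an overlapping symptom. Section 2.6 adds notice to the doctor for usual-care patients, and 5.1.1 itself permits disclosure to physicians on acute decompensation. The two sections can be read together, with 5.1.1 for problems of unclear severity and 5.13 for decompensation. Section 5.1.1 says the call should be made right away, and its word for the first step implies that others follow. The document is also an IRB form answered question by question. Staff are likely to work from call scripts and training, which are not shown and may contain the right rule.

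Most of this stands, and it limits the point to wording. A reader might infer that the protocol has no emergency instruction for chest symptoms; 5.13 shows otherwise. A reader might also infer a flat contradiction. The text does not support that either, since the physician call is one of the options in 5.13 and is listed first. Nor can it be said that neither section conveys severity, because 5.13 presents chest pressure as a sign of decompensation.

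The reply does not remove the rule that 5.1.1 states. That section chooses chest pain as its example and gives it one response, without the emergency options that the sponsor adopted in 5.13.

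**Conclusion.** The point holds as a minor patient-safety correction and a cheap improvement. Read literally, 5.1.1 is less safe than 5.13 for an overlapping symptom reported to the same staff.

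Its size cannot be given as a number. The protocol reports no rate of chest symptoms on calls and nothing on how long a physician-first step would take, so a count of calls would not measure delay. The harm also depends on staff applying 5.1.1 without 5.13, which the document does not show they would do.

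A reader might extend this to bias in the hospitalisation outcomes through uneven ER advice. The protocol does not support that extension: 5.13 already foresees an effect of ER referral and plans to record and adjust for it. No effect on an endpoint, the sample size or an analysis is claimed.

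**What to change.** Amend 5.1.1 so that chest pain or pressure, severe shortness of breath or other signs of acute decompensation voiced on a call are handled under 5.13, with the ER or 911 advised when symptoms are acute or severe. Keep the physician-first advice for non-acute physical problems. The clause on acute or severe symptoms is needed because 5.13 lists its three options without saying when each applies, so a bare cross-reference would leave the order open. Apply the rule to assessors and care managers in all four groups.

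The cost is one or two sentences, a cross-reference and a check that the call scripts agree, with no added staff or procedures. The downside is possibly a few more ER referrals, which 5.13 already plans to record and adjust for.
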